## Abstract

**Background:**

Immune checkpoint inhibitors of programmed cell death protein 1 (PD-1) represent a significant breakthrough in treating head and neck squamous cell carcinoma (HNSCC), with long-lasting responses and prolonged survival observed in first- and second-line therapy. However, this is observed in < 20% of patients and high primary/secondary resistance may occur. The primary objective of the identification of predictive factors for the response to anti-PD-1 immunotherapy in head and neck squamous cell carcinoma (IPRICE) study is to identify predictive factors of response to anti-PD-1 immunotherapy.

**Methods:**

The IPRICE study is a single-center, prospective, non-randomized, open-label, and interventional clinical trial. Liquid and tumor biopsies will be performed in 54 patients with recurrent/metastatic (R/M) HNSCC undergoing anti-PD-1 immunotherapy alone to compare the evolution of gene expression and immunological profile between responders and non-responders. We will use a multidisciplinary approach including spatial transcriptomics, single seq-RNA analysis, clinical data, and medical images. Genes, pathways, and transcription factors potentially involved in the immune response will also be analyzed, including genes involved in the interferon-gamma (IFN-γ) pathway, immunogenic cell death and mitophagy, hypoxia, circulating miRNA-mediated immunomodulation, cytokines, and immune repertoire within the tumor microenvironment (TME). With a follow-up period of 3-years, these data will help generate effective biomarkers to define optimal therapeutic strategy and new immunomodulatory agents based on a better understanding of primary/secondary resistance mechanisms. Tumor biopsy will be performed initially before the start of immunotherapy at the first tumor assessment and is only proposed at tumor progression. Clinical data will be collected using a dedicated Case Report Form (CRF).

**Discussion:**

Identifying predictive factors of the response to anti-PD-1 immunotherapy and optimizing long-term immune response require a thorough understanding of the intrinsic and acquired resistance to immunotherapy. To achieve this, dynamic profiling of TME during anti-PD-1 immunotherapy based on analysis of tumor biopsy samples is critical. This will be accomplished through the anatomical localization of HNSCC, which will allow for the analysis of multiple biopsies during treatment and the emergence of breakthrough technologies including single-cell RNA sequencing (scRNA-seq) and spatial transcriptomics.

**Trial registration:**

Clinicaltrial.gov. Registered April 14, 2022, https://www.clinicaltrials.gov/study/NCT05328024.

## Background

Head and neck squamous cell carcinoma (HNSCC) arising on the mucosal surfaces of the oral cavity, sinonasal cavity, pharynx, and larynx represents the eighth most common cancer worldwide, with an estimated annual incidence and mortality of around 880,000 and 445,000 cases, respectively [1]. Tobacco, excessive alcohol consumption, and human papillomavirus (HPV) infection are the main risk factors of HNSCC. The prognosis for HPV-associated oropharyngeal cancer is more favorable due to a better response to chemotherapy and radiotherapy, and fewer comorbidities [2, 3], whereas the prognosis for recurrent or metastatic (R/M) HNSCC is poor. In 2008, the addition of cetuximab to conventional platinum/5-fluorouracil (5-FU) chemotherapy (EXTREME regimen) improved overall survival as seen in long-term responders, although it was a marginal improvement (48 months progression-free survival (PFS) rate < 3%) [4, 5]. Immune checkpoint inhibitors of programmed cell death protein 1 (PD-1) are an important breakthrough with prolonged duration of response and survival observed in both first- and second-line therapies (5 year-overall survival (OS) rate 15.4% for pembrolizumab monotherapy for the combined positive score (CPS) ≥ 1 arm from the KEYNOTE 048 cohort, Makoto Tahara et al. ESMO 2022) [6, 7]; but, this duration of response is observed in < 20% of the patients. The only predictive marker currently available is the expression of PD-L1, according to the CPS, which has been shown to correlate with survival [7]. However, strong primary/secondary resistance is observed, and tumor response is unpredictable (with an objective response rates (ORR) of 23.3% for pembrolizumab monotherapy in the CPS ≥ 20 arm). Consequently, patients with severe symptoms awaiting an urgent therapeutic response require treatments including chemotherapy to reduce life-threatening progression at the cost of increased toxicity [7]. In addition, a growing number of studies are reporting a long-term survival benefit from cetuximab-based chemotherapy after failure of immunotherapy [8–10]. Therefore, immune checkpoint inhibitors appear to be the only current treatment providing effective clinical responses. These observations underline the main challenge in cancer immunotherapy: optimizing long-term survival requires personalized approaches based on composite biomarkers to define the optimal therapeutic strategy and discover new drugs that can generate immunity in patients who do not have a strong immune response [11]. The development of biomarkers and new therapeutic agents to overcome primary/secondary resistance requires an optimum knowledge of the complex interactions between cancer and the immune system involving molecular and cellular drivers of immune escape. This is considered to be a major challenge facing cancer immunotherapy [11]. However, this objective is complicated by the difficulty of studying not just immune cells but rather an “orchestra of immune and non-immune players” evolving during systemic cancer therapy (Girolami et al. 2023 Journal of Personalized Medicine). Currently, the classification of tumor immunity is almost exclusively based on the spatial distribution of CD8 + T cells in the tumor microenvironment (TME), which are targeted by immune checkpoint inhibitors of PD-1 thereby enhancing their anti-tumor functions [12]. A gradient of three immunophenotypes associated molecular pathways is observed: inflamed tumors including tumor infiltrating lymphocytes (TILs) and B cells in the TME in close proximity to tumor cells; immune-excluded tumors including immune cells distant from tumor cells in the tumor stroma; and immune desert tumors devoid of T cell infiltration. Using gene expression of HNSCC tumor data obtained from The Cancer Genome Atlas (TCGA) database, another immune-infiltrating signature-based classification was recently proposed with three immunophenotypes including other immune cells: cold, lymphocyte (enrichment for CD4 + T cells, CD8 + T cells, and B cells) similar to the previous classification, and myeloid dendritic (DC) signatures (enrichment of neutrophils, macrophages, monocytes, DCs, and T regulatory (Treg) cells) [13]. Thus, classifying TME based on immune cell infiltration alone excludes major actors in cancer immunity such as stromal cells including carcinoma associated fibroblasts (CAF) or tertiary lymphoid structures (TLS) representing promising targets for cancer treatment [14]. Notwithstanding these limitations, classification based on immune cells infiltration provides a reference framework for research describing specific molecular mechanisms for each immunophenotype such as interferon-gamma (IFN-γ) signaling associated with inflamed tumors and transforming growth factor-β (TGF-β) signaling with immune-excluded tumors. Immunotherapy resistance observed in cold tumor may be related to impaired antigen processing (Human leukocyte antigens (HLA) and/or β2 microglobulin loss or downregulation, and elimination of neoantigens through copy-number loss), loss of T-cell priming mainly because of the inhibition of T cells generation by DCs in desert tumor, or the absence of preexisting antitumor T cells infiltration (T-cell-excluded tumors) [15]. Therefore, to enhance antitumor immune responses, next generation immunotherapy should promote lymphocyte activation by tumor antigens and antigen-presenting cells (APC), differentiation and infiltration of lymphocytes in the TME, and tumor cell recognition. However, new therapeutic drugs still have limitations in achieving long-term responses and survival in the majority of patients. This is illustrated in HNSCC by the absence of new therapeutic agents since the arrival of PD-1/PDL-1 blockade drugs and the large number of failures in clinical trials testing combination treatment with immune checkpoint inhibitors in recent years: INDUCE-3 and INDUCE-4 trials investigating feladilimab (inducible T cell co-stimulatory agonist) in combination with pembrolizumab (press release GSK April 14, 2021), INTERLINK-1 study evaluating monalizumab (inhibitor targeting natural killer cells group 2A) in combination with cetuximab (press release Innate pharma Jan 8, 2022), CP-MGA271-06 study with enoblituzumab (anti-B7-H3 mediating antibody-dependent cellular cytotoxicity (press release MacroGenics Jul 8, 2022), Active8 trial with motolimod (TLR8 agonist), and ATHENA trial evaluating the combination of atezolizumab and bevacizumab [16, 17]. Although there are promising studies with drugs targeting immune checkpoint receptors (TACTI-002 Part C: A phase II study of eftilagimod alpha, a soluble lymphocyte-activation gene 3 (LAG-3) protein and pembrolizumab), or immunomodulators (BCA101, bifunctional epidermal growth factor receptor (EGFR)/TGFβ inhibitor and pembrolizumab), these are preliminary studies with a small sample size and a tumor response of less than one in two patients [18, 19].

The immune microenvironment is a dynamic structure in a complex interaction with an evolving cancer, but is affected by specific oncology treatments, particularly the immune checkpoint inhibitors. Therefore, a differential evolution of the TME between responders and non-responders induced by cytotoxic T-lymphocyte–associated antigen 4 (CTLA-4) and PD-1 blockade have been observed in a longitudinal study of metastatic melanoma patients [20]. Significantly, differences in TME composition such as number of CD4 + or CD8 + T cells are increased during on-treatment than before suggesting that predictive biomarkers based on immune signatures should be evaluated in on-treatment tumor samples. Few other recent studies have confirmed temporal changes of the TME during PD-1 inhibitor therapy between immune subpopulations but also for tumor mutational burden, T-cell receptor (TCR) repertoire, immune-related genes, proliferation-associated and chemokine genes, neoantigen immunogenicity landscapes, and tumor clonal populations [21–25]. However, how immune checkpoint inhibitors shape the TME and how they interact with cancer cells remain poorly understood. Therefore, the majority of studies only provide a snapshot of the immune landscape because dynamic profiling of the TME requires biological samples not often available in clinical practice. Profiling of the TME during anti-PD-1 immunotherapy may be essential to accelerate the understanding of the mechanisms that underlie primary and secondary resistance [26–28]. Besides existing immunotherapy, studies also suggest the importance of a deeper understanding of dynamic neoantigen profiles for vaccine development [26]. Targeting antigen selection to ensure high immunogenicity and tumor-specificity is a complex process considering mutation calling, clonality, HLA typing and binding affinity, antigen processing, and similarity to self [29]. Genomic and transcriptomic data may facilitate this selection step by prioritizing the antigens maintained despite tumor evolution and neoantigens silenced in immune-excluded TME [26]. This latter mechanism could explain tumor responses observed on salvage chemotherapy after progression with immune checkpoint inhibitors used in first-line treatment, but our proposal in this study is yet to be investigated [30]. Collecting consecutive clinical tumor biopsies remains a challenge when the treatment is ongoing, suggesting that basic research in cancer immunology and the development of cancer immunotherapy agents are largely based on treatment-naive tumors. However, most patients with incurable HNSCC eligible for immune checkpoint inhibitors had locoregional recurrence occurring in a previously irradiated area, which probably induce a change in TME. However, in the case of HNSCC, tumors are often visible and palpable, and biopsies can therefore be easily processed, allowing a longitudinal TME profiling.

A differential TME-related gene expression analysis between anti-PD-1/PD-L1 immunotherapy responders and patients with a progressive disease requires the use of breakthrough technologies. Indeed, deep analysis of the main cellular subsets including tumor cells, tumor-associated stromal cells, and tumor-infiltrating immune cells should consider their position, their organization in the TME, their state, function and cellular phenotype, their interaction with neighboring cells, and the changes over time caused by immunotherapy. Among these new technologies, single-cell RNA sequencing (scRNA-seq) offers the highest cellular resolution but requires tissue dissociation resulting in the loss of spatial information. Spatial transcriptomics (ST), named “Method of the Year 2020” by Nature Methods, is another powerful technique. It preserves the spatial context of biological data and allow the visualization of gene expression distributions. It is suitable for small samples but is limited by low cellular resolution [31, 32]. Thus, scRNA-seq and ST are two complementary technologies that will be performed in this study. Differential gene expression analysis between responders and non-responders to anti-PD1/PD-L1 immunotherapy will focus on immune-related genes such as immune checkpoint genes, but also on genes that play important roles in TME including hypoxia-related genes, ΔNp63 (potentially implicated in the recruitment of myeloid-derived suppressor cells and overexpressed in HNSCC), immunogenic cell death genes, and mitophagy-related genes, which may be targeted to improve the effectiveness of cancer immunotherapy [33–35]. A particular focus will be made on IFN-γ mediated signaling that may result in both protumoral (immunosuppression, angiogenesis, and tumor cell proliferation) and antitumoral (tumor cell killing, T cell activation, immune cell proliferation, and promotion of antigen presentation) activities indicating the emphasis on its therapeutic modulation [36]. These conflicting activities may be related to the duration and the importance of IFN-γ signaling which are affected by tumor burden, immune cell infiltration characteristics, and cancer treatment (immunotherapies and chemotherapies) [36]. Although producers of IFN-γ and the different effects of IFN-γ in the TME are well documented, lots of questions remain on its involvement in the primary/secondary resistance and on its complete and long-lasting response to immune checkpoint inhibitors. Understanding these mechanisms also requires dynamic analysis of IFN-γ production in the TME undergoing immunotherapy.

Thus, analysis of biopsy samples of patients undergoing immunotherapy might contribute to a better understanding of resistance process but with inherent limitations. These include the invasive nature of the analysis with uncertainties related to patients compliance issues and importantly, the intra-tumor heterogeneity with disparate levels of immune infiltration leading to underestimation of the tumor genomics landscape. Conversely, liquid biopsy may overcome tumor heterogeneity in addition to being noninvasive, allowing continuous monitoring of circulating tumor DNA (ctDNA), circulating tumor cells (CTCs), exosomes, miRNAs, circulating immune cell, and TCR repertoire [37]. Studies have already documented the prognostic ability of ctDNA to detect HNSCC recurrence and/or metastasis [38]. However, there are no prevalent hotspot mutations in HNSCC, only a wide spectrum of mutations including for TP53 tumor suppressor gene which is the most frequent of all somatic genomic alterations in HNSCC [39]. Thus, ctDNA monitoring requires personalized trackable mutations.

The same would apply to miRNAs, a class of endogenous non-coding RNAs involved in post-transcriptional regulation of gene expression and playing an important role in chemo-resistance of cancer cells [40]. Cancer-associated circulating miRNAs are secreted both by immune and tumor cells, suggesting potential predictive value and therapeutic interest [41, 42]. Lastly, understanding the role of circulating cytokines in cancer immunotherapy was a major development that led to the approval of recombinant IFN-α and interleukin (IL)-2 for the treatment of several malignant diseases [43]. Current challenges include suppression of immunosuppressive cytokines, limitation of systemic proinflammatory effects, and to a lesser extent, biomarker development [43]. Thus, tumoral immunity is characterized by a complex interaction between the TME and the peripheral immune system that requires a deeper understanding. Regarding liquid biopsy, the proposed study will focus on the exploration of circulating miRNA-mediated immunomodulation and circulating cytokines.

In this single-center prospective study, we propose to combine liquid biopsy, tissue biopsy, and clinical data at key time points during the management of patients undergoing anti-PD-1 immunotherapy for R/M HNSCC. We will compare the evolution of gene expression profile between responders and non-responders, using spatial transcriptomics analysis among other technologies.

## Methods/design

### Study design

The IPRICE study is a single-center, prospective, non-randomized, open-label, and interventional clinical trial of patients managed at the Cancer Institute of Strasbourg (ICANS) Europe (Strasbourg). Study inclusion period will be 3 years; each patient will be followed up for 3 years and the total study duration will be 6 years. The study design is depicted in Fig. 1. The IPRICE study and this manuscript have been written in accordance with standard protocol items, namely recommendations for interventional trials (SPIRIT).

**Fig. 1 Fig1:**
[figure not shown]
IPRICE study design

### Study objectives and endpoints

The main objective of this study is to identify effective biomarkers of response to PD-1 checkpoint blockade using combinatorial omics analysis including spatial transcriptomics, scRNA-seq, and miRNomics. The primary endpoint is the prospective validation of the IFN-γ–related gene expression signature to predict response to PD-1 checkpoint blockade (overall response including complete response (CR) and partial response (PR)). Tumor response was defined according to the Response Evaluation Criteria In Solid Tumor (RECIST) criteria. Secondary outcomes are the prospective validation of potential response biomarkers (immunogenic cell death and mitophagy-related markers, expression of hypoxia-related markers, and circulating miRNA-mediated immunomodulation). Exploratory outcome measures will include dynamic and differential profiling of the immune repertoire in the TME between responders and non-responders.

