#### Profiling circulating miRNA from liquid biopsies

The miRNAs will be extracted from 200 μl of cell-free plasma using the miRNeasy serum/plasma extraction kit (Qiagen) according to the manufacturer’s instructions. RNA quality will be assessed using a Nanodrop Spectrophotometer (Thermo Scientific), resulting in a mean 260/280 ratio of 1.95. RNA will be processed for miRNA-sequencing and RT-qPCR. The sequencing of miRNAs extracted from the serum through liquid biopsy will be performed by Qiagen, a leading provider for RNA studies. The study will include sample quality control using qPCR, library construction and quality control, miRNA sequencing, and analysis of the results.

As a complement, digital PCR (dPCR) based on the partitioning of the sample into thousands of micro-reactions of defined volume will be performed with miRNA of interest because of higher precision and sensitivity to detect low-abundance miRNAs in plasma samples [45].

The potential predictive value of miRNAs signature will be validated. In addition, optimal expression cutoff values will be determined using receiver operating characteristic (ROC) curve analysis to determine the relationship between miRNAs signature and Overall Response Rate (ORR; used as an endpoint). Hazard ratios will be adjusted in multivariate models including the principal known confounding prognostic factors, such as patient age, tobacco smoking, treatment, co-morbidities, margin status, extra-capsular status, tumour localization, differentiation, stage, lymph node involvement, and tumor size.

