#### Panel of immune-related genes and signatures expression analysis (non-exhaustive list)

DEG analysis between responders and non-responders to anti-PD1/PD-L1 immunotherapy will be performed including:IFN-γ mediated signalingStimulatory (CD27, CD28, CD40, OX40, glucocorticoid-induced TNFR-related protein (GITR), inducible costimulator of T cells (ICOS),…) and Inhibitory (PD1, B7-H3, B and T lymphocyte attenuator (BTLA), cytotoxic T lymphocyte antigen 4 (CTLA-4), indoleamine 2,3-dioxygenase (IDO), killer cell immunoglobulin-like (KIR), lymphocyte-activation gene 3 (LAG3), T-cell immunoglobulin and mucin domain 3 (TIM3), V-domain Ig suppressor of T cell activation (VISTA),…) immune checkpoint genesHypoxia-related genes (Hypoxia-inducible factor (HIF)-1α; HIF-2α,…)ΔNp63 (p40) gene expression signatureImmune cell gene signaturesImmunogenic cell death (Calreticulin, p-eukaryotic initiation factor 2α (eIF2α),…) and mitophagy-related markers (Bcl-2 interacting protein 3 (BNIP3),…)

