### Statistical analysis

Primary endpoint will be the measure of response to PD-1 checkpoint blockade (overall response, CR, and PR) in patients with IFN-γ–related gene expression signature. The expected response rate in patients with IFN-γ–related gene expression signature is 60%, the expected two-sided alpha error is 0.05 and beta error is 0.2, the required number of patients is calculated to be 54 based on the exact binomial test (Casagrande et Pike) and considering the patients excluded from the analysis due to censoring. DEG analysis between responders and non-responders will be performed using DESeq2 package. IFN-γ–related gene expression signature and other genes include in the panel will be considered differentially expressed if log 2-fold change is at least ± 2 and *p*-adjusted value ≤ 0.05.

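### The secondary marker sets are promised as validated, but the methods the article gives for them are discovery methods, most plainly the miRNA cutoffs

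*Protocol article*

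**What the plan says.** All references are to the protocol article.

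- **Study objectives and endpoints** sets three tiers. The primary: "The primary endpoint is the prospective validation of the IFN-γ–related gene expression signature to predict response to PD-1 checkpoint blockade". The secondary tier: "Secondary outcomes are the prospective validation of potential response biomarkers (immunogenic cell death and mitophagy-related markers, expression of hypoxia-related markers, and circulating miRNA-mediated immunomodulation". The third tier: "Exploratory outcome measures will include dynamic and differential profiling of the immune repertoire in the TME between responders and non-responders". The same section gives the main objective as identifying biomarkers of response.
- **Profiling circulating miRNA from liquid biopsies** states: "The potential predictive value of miRNAs signature will be validated". It then adds that optimal expression cutoffs will be found by ROC analysis against overall response. It describes no second cohort and gives no error rate.
- The gene list that holds the hypoxia, immunogenic cell death and mitophagy genes is headed "Panel of immune-related genes and signatures expression analysis (non-exhaustive list"), and several of its entries end in an ellipsis.
- **Statistical analysis** gives the design error rates in the sample-size sentence for the IFN-γ endpoint: "the expected two-sided alpha error is 0.05 and beta error is 0.2". It also sets a rule for the signature and the panel: "other genes include in the panel will be considered differentially expressed if log 2-fold change is at least ± 2", together with an adjusted p-value of at most 0.05.

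**The concern.** Validation means that a marker, its score and its threshold were settled beforehand and are now tested on patients who played no part in choosing them. The article makes that claim for the secondary sets in the same terms as for the primary. It had an exploratory label available and did not use it for them. The steps it describes do not fit the claim, since the marker list is printed as open and the miRNA threshold is to be optimised against the outcome that it should predict.

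At stake is what the trial may conclude. A hypoxia, cell-death or miRNA result from these 54 patients could be reported as prospectively validated, on a par with the IFN-γ result, when it is a first estimate that still needs confirmation elsewhere.

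**Working it through.** **1. What the trial is sized for.** The stated figure is 54 patients, from a 60% response rate in signature-positive patients, two-sided alpha 0.05 and power 0.80. The comparator rate, group split and exclusion allowance are not given, so 54 cannot be strictly reproduced. Assume 60% against 20% in equal groups.

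- Uncorrected n per group = [1.96·√(2·0.4·0.6) + 0.8416·√(0.6·0.4 + 0.2·0.8)]² / 0.4² = (1.358 + 0.532)² / 0.16 = 22.3.
- With continuity correction: (22.3/4)·[1 + √(1 + 4/(22.3·0.4))]² = 27.1, so 28 per group and 56 in total.
- With a 19% comparator the total is 52.

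The figure of 54 is therefore plausible for one primary comparison before any allowance for exclusions. No secondary marker enters it.

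**2. Claim and method side by side.**

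| Set | Claim | Method described |
|---|---|---|
| Immunogenic cell death, mitophagy, hypoxia | validation | responder versus non-responder expression, from a panel printed as non-exhaustive; adjusted p ≤ 0.05 and log2 fold change of at least ±2 per gene; no statement of what makes a set validated |
| Circulating miRNA | validation | signature related to response; cutoff optimised by ROC on response; no error rate, no separate cohort described |

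**3. Tissue sets: why no error rate can be given.** The adjustment method and the family of genes are not stated. Assume a Benjamini-Hochberg adjustment, 30 null genes in the secondary tissue sets, any passing gene counted as a false claim, and the fold-change cut ignored. Simulation then gives the chance of at least one false claim:

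- 60-gene panel with 0, 10 or 20 truly different genes: 2.6%, 25%, 41%.
- About 18,000 genes with 0, 100, 500 or 2,000 truly different genes: 0%, 1.1%, 4.6%, 16%.

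The fold-change cut can only lower these. The answer runs from near 0% to about 40% on inputs that the article does not fix, so no single figure is defensible.

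**4. miRNA: the effect of a data-chosen cutoff.** Assumptions: 54 patients, all with a usable sample; 8 to 16 responders (8/54 = 15%, 16/54 = 30%, which brackets the response rates of under 20% and 23.3% quoted in the article); one miRNA score with no relation to response. The cutoff maximises sensitivity + specificity − 1 (Youden), and Fisher's exact test at two-sided 0.05 is then applied to the same patients. With 40,000 simulated trials per row:

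| Responders | Direction fixed beforehand | Direction free |
|---|---|---|
| 8 | 11.5% | 22.7% |
| 11 | 13.7% | 26.3% |
| 13 | 12.9% | 25.0% |
| 16 | 13.8% | 26.4% |

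A separate simulation under the same assumptions gave 11% to 16% and 23% to 29%. As a benchmark, a cutoff fixed beforehand at the median rejected in at most 4.0% of trials in every row. The excess therefore comes from choosing the cutoff on the outcome. This is for a single score; searching among many miRNAs would add to it.

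**The case against.** **The article condenses a fuller protocol.** An order or alpha split among secondary outcomes commonly sits in the full protocol or the analysis plan, neither of which is shown. This stands: the absence of such a split is no finding. The non-exhaustive heading may likewise only abbreviate a closed list held elsewhere. That is possible, but the printed claim of validation would still rest on a list that the reader cannot see to be closed.

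**The wording is hedged.** The article speaks of potential biomarkers and potential predictive value. That softens the claim. It does not remove it, because the verb is the one used for the primary and the exploratory tier excludes these sets.

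**The ROC cutoff may not be the validation test.** The article introduces the cutoffs as an additional step, and it does not say that they will be tested on the same patients. This also stands, which is why the miRNA range is conditional.

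**Stronger readings that the documents do not support.**

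- A reader might infer that the chance of a false validation is well above 5%: 1 − 0.95³ = 14.3% for three sets, or 1 − 0.95⁴ = 18.5% for four. Those figures need one independent, unadjusted 0.05 test per set, which is stated nowhere. The tissue genes face an adjusted p-value and a fold-change cut.
- A reader might infer that there is no hierarchy. The primary, secondary and exploratory tiers are explicit.
- A reader might count a test at each of the 10 plasma samples per patient. The article does not say that response is tested at each one.

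**Conclusion.** The point holds as a mismatch between claim and method in the printed text. The secondary sets are called validated, while the article's own procedures for them identify markers and choose thresholds on the trial's own patients. The design alpha and the sample size belong to the IFN-γ primary.

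For the tissue sets no size can be attached. For miRNA, a false-positive rate of roughly 11% to 29% instead of 5% follows if a data-chosen cutoff is tested on the same patients. It rests on that assumption, on 8 to 16 responders among 54, and on a single null score; the upper part of the range also needs the direction of effect to be left open. It is an illustration of optimism from cutoff selection, not an error rate of the plan as stated. Nothing here bears on the validity of the IFN-γ primary test.

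**What to change.** 1. In Study objectives and endpoints, describe the secondary outcomes as exploratory, hypothesis-generating evaluation of the named marker sets, and state that the IFN-γ primary is the only confirmatory test, at two-sided 0.05.
2. In the section on profiling circulating miRNA, say that the predictive value of the signature will be explored, and present the ROC cutoffs as estimates that need validation in independent patients.

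This needs no extra patients, samples or assays. The price is a more modest claim for the secondary markers. Should the sponsor want a confirmatory secondary claim, a closed marker list with a gated, multiplicity-adjusted test is one option, but this point does not require it.
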